### Outcomes and measurements

#### Aim 1

To describe MDR/RR-TB treatment outcomes in German TB centres and to analyse known and discussed factors (covariates) associated with treatment discontinuation. The primary outcome measure for Aim 1 is treatment outcome at the end of MDR/RR-TB treatment, according to the updated WHO definitions.^24^ Successful treatment outcomes include ‘treatment completed’ and ‘cured’. ‘Treatment completed’ applies to patients who finish treatment according to guidelines without falling into the category of unsuccessful treatment, while ‘cured’ requires sustainable microbiological conversion of sputum cultures. Unsuccessful treatment outcomes include ‘died’, ‘treatment failed’, ‘lost to follow-up (LTFU)’, and ‘not evaluated’. Follow-ups after treatment completion are not included in this definition and will not be part of the primary analysis. Nevertheless, during post-treatment follow-ups (T3) relapses will be documented. Treatment interruptions of more than 2 months classify as treatment discontinuation, and if no further information on disease progression or whereabouts is available, patients are classified as LTFU. The category ‘not evaluated’ includes patients where no treatment outcome is assigned due to relocation.^24^ For transfers within the study cohort, data collection will continue until a definitive outcome is documented.

Covariates are used for cohort characterisation and as independent or confounding variables in the statistical analysis. They were selected based on known risk factors for unsuccessful treatment and discontinuation in the literature^5–9^ such as demographic data (e.g., age), health-related factors (e.g., smoking, alcohol use, drug use, comorbidities, and co-infections), and clinical as well as microbiological parameters like the extent of TB disease and sputum smear positivity. Additional covariates represent suspected risk factors, like social determinants and structural barriers, discussed in a preparatory workshop with a diverse group of stakeholders in German public health, clinics, ambulatory care, and social work. These include social determinants such as residency status, socio-economic status, living conditions, and insurance coverage (Table).

**Table. tbl1:** Study aims, collected outcomes variables, and corresponding time of data collection in the No1Lost MDR/RR-TB cohort study.

Aims	Outcomes variables	Prospective cohort		
		T0	T1	T2, T3
1. To describe MDR/RR-TB treatment outcomes and to analyse known and discussed risk factors (covariates) associated with treatment discontinuation.	MDR-TB treatment outcome^**A**^		X	X
	Treatment completed, cured, died, treatment failed, lost to follow-up, not evaluated			
	Demography	X		
	Age, gender, height, weight			
	Health-related data	X	X	
	Smoking habit, alcohol consumption,^**B**^ drug use, body mass index (BMI), pregnancy, comorbidities (respiratory-, cardiovascular-, liver-, kidney-, psychiatric-, rheumatologic diseases, malignancies, diabetes), co-infections (HIV, hepatitis B and C), solid organ or stem cell transplantation, others			
	Social determinants	X	X	
	Country of birth, migration background, religion and residency status,^**C**^ language/reading skills, socio-economic status^**D**^ (education, occupational qualification, employment, financial resources), living conditions, marital status, social environment at treatment location, insurance status, others			
	TB history and risk	X		
	Previous TB episodes, residence in high-burden country,^**E**^ imprisonment, contact with infectious TB case, BCG vaccination status, use of biologicals, others			
	TB symptoms	X	X	X
	Fever, night sweat, unintentional weight loss, pain, shortness of breath, oxygen saturation, cough enlarged lymph nodes, symptom duration			
	TB drug resistance	X	X	X
	Phenotypic and genotypic resistance testing including sequencing data			
	Infection control		X	
	Isolation measures and duration			
2. To evaluate and compare outcomes and safety of different MDR/RR-TB treatment regimens in German TB centres.	MDR-TB treatment regimens	X	X	X
	BPaL, BPaLM, other 6- to 9-month regimens, individualised treatment			
	Adverse events^**F**^		X	X
	Allergic reactions, skin discolouration, polyneuropathy, impaired vision, nausea, psychological alterations, hepatotoxicity, prolonged QTc time, anaemia and other forms of myelosuppression, renal insufficiency, others			
	Complications		X	X
	TB immune constitution syndrome (TB-IRIS), others			
3. To evaluate guideline adherence.	Covariates and treatment data will be used to decide on performance indicators based on relevance, scientific soundness, and feasibility.	X	X	X
4. To characterise the relevant structures for MDR/RR-TB treatment in Germany.	Treatment structure	X	X	
	Geographical location/region, level of care,^**G**^ number of hospital beds, hospital type,^**G**^ sponsorship,^**G**^ specialised medical departments for MDR/RR-TB treatment, leisure activities/social support for TB patients, language and culture mediation, local network structures, use of assessment tools during treatment (i.e., questionnaires for QoL, psychological stress, and symptoms), others			
5. To characterise the relevant structures for MDR/RR-TB treatment in Germany.	Diagnostic imaging	X	X	X
	Imaging for pulmonary and/or extra-pulmonary TB			
	Laboratory diagnostics	X	X	
	ALT/ALAT, AST/ASAT, GGT, bilirubin, creatinine, haemoglobin, platelets, leukocytes, TSH, QTc time, albumin, interferon-gamma release test, SARS-CoV-2 RNA, streptococcus pneumoniae, legionella pneumophila, others			
	Pathogen diagnostics	X	X	
	Sputum diagnostics (microscopy, PCR, culture), bronchoscopic interventions, CT-guided biopsies, others			

Time points: T0 = baseline; T1 = discharge; T2 = follow-up after discharge; T3 = follow-up after treatment completion.

ALT/ALAT = alanine transaminase; AST/ASAT = aspartate transaminase; BCG = Bacillus Calmette–Guérin; BPaL = bedaquiline, pretomanid, and linezolid; BPaLM = bedaquiline, pretomanid, and moxifloxacin; CT = computer tomography; GGT = gamma-glutamyltransferase; HIV = human immunodeficiency virus; MDR-TB = multidrug-resistant TB; MRI = magnet resonance imaging; PCR = polymerase chain reaction; PET = positron emission tomography; QoL = quality of life; QTc = duration from the onset of the Q wave to the end of the T wave in the heart’s electrical activity; RNA = ribonucleic acid; SARS-CoV-2 = severe acute respiratory syndrome coronavirus type 2; TSH = thyroid-stimulating hormone.

A
WHO treatment outcome definition, updated in 2021.^24^

B
Alcohol Use Disorders Identification Test (AUDIT-C).^25^

C
RKI recommendations for collecting and analysing migration-related determinants in public health research.^26^

D
RKI recommendations for calculating index of socio-economic status.^27^

E
WHO global list of high-burden countries for TB, HIV-associated TB, and drug-resistant TB.^28^

F
The Division of Acquired Immunodeficiency Syndrome (DAVIS) table for grading the severity of adult and paediatric adverse event.^29^

G
German Federal Ministry of Health classification for inpatient care facilities.^30^

#### Aim 2

To describe the use, outcomes, and safety of different MDR/RR-TB treatment regimens in German TB centres. Outcomes relevant to Aim 2 include the above mentioned MDR/RR-TB treatment outcome according to WHO definitions^24^ depending on different MDR/RR-TB treatment regimens. Safety will be monitored through systematic documentation of adverse events (e.g., allergic reactions, skin discolouration, polyneuropathy, impaired vision, nausea, psychological alterations, hepatotoxicity, prolonged QTc time, anaemia and other forms of myelosuppression, and renal insufficiency), as well as major complications such as TB-IRIS. Clinical laboratory data and imaging results will support the safety evaluation. The Division of Acquired Immunodeficiency Syndrome (DAVIS) table for grading the severity of adult and paediatric adverse event was used for safety evaluation.

#### Aim 3

To describe adherence to German TB guidelines and explore possible barriers in the participating TB centres. A set of performance indicators will be selected by a panel of guideline authors based on relevance, scientific soundness, and feasibility as described by the Association of the Scientific Medical Societies in Germany (AWMF)^31^ for Aim 3. Staff Interviews based on the results of interim analyses will be used to generate qualitative data to explore reasons and possible barriers for non-adherence to German guidelines.

#### Aim 4

To describe the clinical treatment structures for MDR/RR-TB treatment in the participating TB centres. Covariates relevant to Aim 4, such as hospital size, geographical setting (urban/rural), local network structures, hospital sponsorship, the availability of specialised departments for MDR/RR-TB treatment and facilities for TB treatment and support, infection control measures, and the use of assessment tools, for example, for quality of life, will be used to describe MDR/RR-TB-treatment structures in the participating TB centres. A comprehensive overview of outcomes, covariates, and the corresponding time points of data collection (T0–T3) is provided in Table.

### Data management

CAPNETZ STIFTUNG with its well-established structure for conducting clinical studies in Germany will be responsible for data management with support of the No1Lost study team.^32^ Study data is stored in the Electronic Data Capture (EDC) system, designed for data collection, management, and monitoring in multi-centre clinical trials. It includes a web-based data entry module, plausibility checks, reporting tools, and a query management system that complies with Good Clinical Practice and FDA 21 CFR Part 11 standards. Protocol-based case report forms (CRFs) are programmed into the EDC system with functional pre-testing prior to data collection. Each study site receives virtual training and optional on-site support. Throughout the study, CRF entries are monitored online for completeness and content discrepancies. Interim analyses will ensure efficient data processing and data quality, including missing value analysis, and are conducted at the end of the first and second year of the study. Summary reports on recruitment status, case numbers, and data quality will be shared with study partners and the clinical network to ensure transparency and collaboration between the study team and TB sites.

### Statistical analysis

Main outcomes (defined in aims 1–4 above: 1) MDR/RR-TB treatment outcome, 2) outcomes and safety of different MDR/RR-TB regimens, 3) guideline adherence, and 4) relevant structures for MDR/RR-TB treatment) as well as covariates (demographic, health-related, sociomedical, and clinical parameters) will be analysed using descriptive statistics. Nominal data will be presented with absolute and relative frequencies, continuous data with means and standard deviations (±SD), and ordinal or skewed data with medians, first and third quartiles (Q1 and Q3). The sample size was calculated to ensure adequate precision for estimating the primary outcome of treatment discontinuation. Based on previous data,^11^ we anticipate a discontinuation rate of approximately 25%. To estimate this proportion with a 95% confidence interval (CI) margin of error of 7.5% or less, a sample of at least 129 patients is required. Our expected enrolment of approximately 150 MDR/RR-TB patients is therefore feasible and exceeds this minimum requirement. With this sample size, we will be able to estimate an observed rate of 25% with a 95% CI of 18.1%–31.9% (margin of error 6.9%). This level of precision is considered sufficient for the study’s primary objectives of informing future programme planning and intervention design (powermediation package in R). In an exploratory analysis, MDR/RR-TB treatment outcome will be modelled as a binary dependent variable in generalised linear models (e.g., logistic regression) to quantify the effect of relevant demographic, sociomedical, and clinical factors on treatment discontinuation (yes/no). The WHO categories ‘LTFU’ and ‘not evaluated’ will be combined and classified as treatment discontinuation. Effect sizes, such as odds ratios with 95% CIs, will be calculated and reported. To account for clustering effects at the TB centre level, we will also employ generalised estimating equations. All statistical tests will be two-sided, and robust standard errors will be applied to improve variance estimation. A significance threshold of *P* < 0.05 will be used, with adjustments for multiple testing when necessary.

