Germany is a low-incidence country for TB with a high-resource health care system. Nevertheless, treatment success for TB remains below WHO targets with 63% in 2022.^1,2^ Inconclusive treatment results due to patients transferred to unknown destinations (5.1%) or treatment discontinuation for other reasons (3.2%) are major drivers for unsuccessful TB treatment results.^3^ Early TB treatment discontinuation increases the risk of treatment failure, antibiotic resistance, and transmission of resistant TB strains.^4^ Factors associated with TB treatment discontinuation include older age, alcohol and drug use, poor health literacy, drug adverse events, treatment length, and lack of social support, especially in contexts marked by socio-economic, legal, and structural challenges, such as homelessness and uncertain immigration status.^5–10^ However, published data mainly originate from countries with high TB incidence and cannot always be applied to low-incidence health care settings. To our knowledge, no prospective studies examining the impact of social determinants on TB treatment outcomes have been conducted in high-income, low-incidence settings. Multidrug- or rifampicin-resistant TB (MDR/RR-TB) patients are at increased risk of treatment discontinuation.^4^ A retrospective analysis of two German treatment centres showed 25% inconclusive treatment outcomes due to transfer and loss to follow-up (LTFU) with individualised MDR/RR treatment of 20 months (median).^11^ Shorter and more tolerable regimens like BPaL/M (bedaquiline, pretomanid, and linezolid with or without moxifloxacin) promise fewer side effects and higher rates of treatment completion.^12,13^

Since 2022, the WHO guidelines prioritise the use of the 6-month BPaL/M regimens for treatment of MDR-TB. Despite challenges with the implementation of this pretomanid-containing regimen, the recommendation was adopted for MDR/RR-TB in Germany in 2023.^14^ Other shortened 6- and 9-month treatment regimens based on the results of EndTB^15^ and BEAT-TB^16^ trials were included in the updated WHO guidelines 2025, and further adoption of national guidelines will be necessary.^17^ Recent study data and the evolution of guidelines will lead to a variety of different treatment options for MDR/RR-TB. However, data on the impact of shortened regimens like BPaLM on treatment outcomes and adherence in low-incidence countries are limited^18^ and not yet available for the new 6- and 9-month treatment regimens.

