### Data collection

For the prospective cohort, routine clinical data concerning TB disease and treatment, along with demographic, sociomedical, radiology, microbiology, and laboratory data, will be collected at hospital admission (baseline, T0) and discharge (T1). During outpatient treatment, follow-up data will be collected every 3 months, restricted to TB treatment, radiology, and microbiology data until a treatment outcome is documented (T2). Post-treatment follow-ups occur every 6 months after treatment completion and include data on outcome changes, recurrence, and post-TB lung disease (T3) (Figure).

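### Adverse event percentages by regimen cover different lengths of exposure, so add exposure-adjusted or common-window figures beside them

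*Protocol article*

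**What the plan says.** Aim 2 is worded in two ways. The Table in Outcomes and measurements has "To evaluate and compare outcomes and safety of different MDR/RR-TB treatment regimens in German TB centres", whereas the text under Aim 2 has "To describe the use, outcomes, and safety of different MDR/RR-TB treatment regimens in German TB centres". Study objectives also says only that these features will be described.

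The regimen groups in the Table are "BPaL, BPaLM, other 6- to 9-month regimens, individualised treatment". The introductory text gives two durations. One is for the short regimens: "the WHO guidelines prioritise the use of the 6-month BPaL/M regimens for treatment of MDR-TB". The other comes from an earlier retrospective series at two German centres, "with individualised MDR/RR treatment of 20 months (median").

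The Statistical analysis section assigns the Aim 2 outcomes to descriptive statistics. The rule for categorical variables is "Nominal data will be presented with absolute and relative frequencies". No person-time rate, common time window or time-to-event summary is named.

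On the observation period, Data collection has outpatient follow-up every 3 months "until a treatment outcome is documented (T2"). The main outcome is "treatment outcome at the end of MDR/RR-TB treatment", so it too is assessed when each patient's own course ends.

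The documents differ on when adverse events are collected. Data collection limits the T2 visits to treatment, imaging and microbiology data, and for T3 it lists outcome changes, recurrence and post-TB lung disease. The Table nevertheless marks adverse events at T1 and in the joint T2, T3 column.

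**The concern.** The proportion of patients with at least one adverse event grows with time under observation. If a 6-month group and a much longer individualised group are set side by side as percentages, part of any difference may reflect months of exposure rather than risk per month on the drugs.

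This matters because the introductory text says that shorter regimens promise fewer side effects, and that data on them in low-incidence countries are limited or not yet available. A crude table could seem to confirm that promise through exposure time alone. Whether it would be read that way depends on whether Aim 2 compares or only describes, and the article says both.

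**Working it through.** **The plan's own figure.** The article gives no calculation for safety by regimen. Its only calculation is the precision target for discontinuation, which reproduces: n = 1.96² × 0.25 × 0.75 / 0.075² = 128.05, rounded up to 129. At n = 150 the margin is 1.96 × √(0.25 × 0.75 / 150) = 6.9 points, giving 18.1% to 31.9%. Nothing below changes these figures.

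**Inputs.**
- Durations of 6 and 9 months are the article's lengths for the shortened regimens.
- 20 months is the median in the earlier series. It is used as an illustration of a long course, not as this cohort's planned duration.
- The monthly adverse event risk *r* is not in the documents. It is assumed equal in every regimen and varied from 1% to 10%.

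**Constant risk.** The percentage with at least one event by month *t* is 1 − exp(−*r t*). For example, at 1% per month and 6 months it is 1 − exp(−0.06) = 5.8%.

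| Monthly risk, same in all regimens | 6 months | 9 months | 20 months | Ratio 20 to 6 |
|---|---|---|---|---|
| 1% | 5.8% | 8.6% | 18.1% | 3.1 |
| 2% | 11.3% | 16.5% | 33.0% | 2.9 |
| 5% | 25.9% | 36.2% | 63.2% | 2.4 |
| 10% | 45.1% | 59.3% | 86.5% | 1.9 |

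The 9 to 6 month ratio, which does not need the historical 20-month figure, runs from 59.3 / 45.1 = 1.3 to 8.6 / 5.8 = 1.5. A rate per patient-month, or a percentage within the first 6 months, would be equal across regimens in every row.

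**Front-loaded risk.** Assume 5% per month for 3 months and a lower late risk *l* afterwards. The percentage is 1 − exp(−[0.15 + *l*(*t* − 3)]).

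| Late risk per month | 6 months | 9 months | 20 months | Ratio 20 to 6 |
|---|---|---|---|---|
| 0 | 13.9% | 13.9% | 13.9% | 1.0 |
| 0.5% | 15.2% | 16.5% | 20.9% | 1.4 |
| 1% | 16.5% | 18.9% | 27.4% | 1.7 |

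**Discontinuation, for contrast.** A 25% loss over 20 months corresponds to a constant hazard of −ln(0.75) / 20 = 1.44% per month. The same hazard gives 8.3% over 6 months and 12.1% over 9 months. Here the difference is a true consequence of a longer course: more patients fail to finish it.

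**The window itself.** If adverse events are collected only to discharge, as the Data collection text would imply, the window is the hospital stay and the calculation above does not describe it. If they are collected through T2, the window follows regimen length. If T3 counts as well, observation continues after a short course ends and the gap narrows. The article supports more than one of these readings.

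**The case against.** The quoted sentence is a general rule for all categorical variables in all four aims. It does not say that adverse events will appear only as percentages, and descriptive statistics do not exclude rates. Aim 2 is secondary, and a condensed article commonly leaves denominators and the handling of regimen changes to the analysis plan. This stands so far as it goes: the absence of those details is not itself a finding. But the article does state a summary method and, in the Table, a comparative aim, and that method does not suit that aim when exposure differs.

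The magnitude rests on assumed inputs. This also stands. No event rate or timing is given, and 20 months is historical.

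A reader might go further and infer three things that the documents do not support:
- *That longer regimens would look worse merely because of exposure.* The effect vanishes if events come early, and the percentage per course is a legitimate description of burden.
- *That the comparison of retention is distorted in the same way.* The WHO outcome is defined at the end of treatment, and the introductory text lists treatment length among the factors associated with discontinuation. Greater loss over a longer course is part of the study question, and dividing it by person-time would hide it.
- *That events will be moved away from the regimen that led to a switch.* Regimen is recorded repeatedly, but nothing says that results will be tabulated by regimen received. Those records serve attribution by starting regimen equally well.

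**Conclusion.** The point holds for adverse events only. With frequencies as the stated summary, observation that follows regimen length and a Table that promises comparison, crude percentages can differ between regimens partly through exposure time. At equal risk per month and within the treatment period, the longer regimen never gains from this.

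For 6 against 20 months, the ratio of crude percentages at equal risk is about 1.9-3.1 under constant risk of 1-10% per month, about 1.4-1.7 in the front-loaded examples, and 1.0 if all events come early. No single value should be presented as the expected distortion. The result assumes that adverse events are recorded throughout treatment, which the article leaves inconsistent.

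This is a worthwhile improvement to a secondary, descriptive aim. It affects neither the sample size nor the primary outcome.

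**What to change.** 1. For adverse events, tabulate by the regimen started. Beside the raw counts and percentages, give either event rates per 100 patient-months on treatment with 95% CI, or the cumulative incidence within a common window such as the first 6 months. Report regimen switches separately.
2. Keep per-course percentages for the WHO outcomes, including discontinuation.
3. Reconcile the Table's wording of Aim 2 (evaluate and compare) with Study objectives and the Aim 2 text (describe). State that differences between regimens are not adjusted for indication.
4. Reconcile Data collection with the Table on whether adverse events are recorded at T2 and T3, so that the adverse event window is defined.

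The cost is one more table, and adverse event onset dates together with regimen start and stop dates. The article does not show that onset dates are collected, so the case report form should be checked. Estimates will be imprecise in small groups. If 150 patients split evenly over the Table's four regimen categories (an assumption), each has about 37.5, and a 25% proportion carries a margin of 1.96 × √(0.25 × 0.75 / 37.5) = 13.9 points.

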## METHODS

### Study design

This is a prospective, observational, multi-centre cohort study. Patients will be observed from January 2025 to December 2027 in German TB treatment centres, recruited from a network of at present 72 clinics available for MDR/RR-TB treatment.^23^ After assessment of feasibility, including number of MDR/RR-TB patients in the last 5 years and prerequisites for successful study implementation, 23 TB treatment centres have been recruited for the study to date. Based on prior case notifications, we expect to enrol approximately 150 patients into the prospective cohort.

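### The 6.9-point margin and the minimum of 129 assume independent patients, although the same section expects clustering by centre; the 7.5-point target is missed above an assumed ICC of about 0.02–0.03

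*Protocol article*

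**What the plan says.** In the protocol article, the Statistical analysis section sizes the study for one proportion, treatment discontinuation: "we anticipate a discontinuation rate of approximately 25"%. The requirement is worded as "To estimate this proportion with a 95% confidence interval (CI) margin of error of 7.5% or less", and the result is that "a sample of at least 129 patients is required". Enrolment of about 150 is then said to be above that minimum, and the section adds that "we will be able to estimate an observed rate of 25% with a 95% CI of 18.1%–31.9% (margin of error 6.9"%). It judges this precision sufficient for planning future programmes and interventions. No ICC, design effect or other allowance for centres appears.

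Later in the same section, for the exploratory regression, the article says: "To account for clustering effects at the TB centre level, we will also employ generalised estimating equations". It adds that "robust standard errors will be applied to improve variance estimation". The Study design section says that "23 TB treatment centres have been recruited for the study to date", drawn from a network of 72 clinics.

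**The concern.** The precision statement and the analysis statement rest on different assumptions. If patients of one centre resemble each other in whether they discontinue, 150 patients carry less information than 150 independent ones, and an interval from the binomial formula is too narrow. Some resemblance is plausible here, because the study sets out to describe how treatment structures and support differ between centres.

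The discontinuation proportion and its interval are the only quantities for which the article sets a precision target. If the published interval is computed as the sample size section implies, it will overstate what is known about discontinuation in German MDR/RR-TB care. The sentence placing 150 above the minimum would also reassure readers without stating the condition it depends on.

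**Working it through.** **Inputs from the article.** Anticipated proportion p = 0.25, 95% confidence, target margin 7.5 points, stated minimum 129, expected enrolment 150 (all Statistical analysis); 23 centres to date (Study design). Mean centre size m = 150/23 = 6.52.

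**Inputs assumed.** ICC on the response scale, 0.01 to 0.10, and CV of centre size, 0 (equal) to 0.8. The article gives neither.

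**Step 1: reproduce the stated figures.**
- n = z²p(1−p)/d² = 1.96² × 0.1875 / 0.075² = 128.05, rounded up to 129. This matches.
- Margin at 150 = 1.96 × √(0.1875/150) = 6.93 points, so the interval is 18.07% to 31.93%. This matches.

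Both formulas treat patients as independent.

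**Step 2: how much clustering 150 patients can absorb.** The largest tolerable design effect is 150/128.05 = 1.17.

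**Step 3: design effect.** DE = 1 + [m(1 + CV²) − 1] × ICC, and margin = 6.93 × √DE. The bracket is 5.52 for CV 0, 7.15 for CV 0.5 and 9.70 for CV 0.8.

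| ICC | DE (CV 0 to 0.8) | Margin, points | Effective N |
|---|---|---|---|
| 0.01 | 1.06 to 1.10 | 7.1 to 7.3 | 142 to 137 |
| 0.02 | 1.11 to 1.19 | 7.3 to 7.6 | 135 to 126 |
| 0.03 | 1.17 to 1.29 | 7.5 to 7.9 | 129 to 116 |
| 0.05 | 1.28 to 1.48 | 7.8 to 8.4 | 117 to 101 |
| 0.10 | 1.55 to 1.97 | 8.6 to 9.7 | 97 to 76 |

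**Step 4: where the target is lost.** Setting DE = 1.171 gives ICC = 0.171/5.52 = 0.031 (equal centres), 0.171/7.15 = 0.024 (CV 0.5) and 0.171/9.70 = 0.018 (CV 0.8).

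These margins keep z = 1.96 so that they compare directly with the article. A t reference with 22 degrees of freedom would widen each by 2.074/1.96 = 1.058, about 6%.

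**Step 5: coverage of the unadjusted interval.** I simulated 150 patients in 23 centres with beta-distributed centre rates averaging 25% (20,000 studies per setting). The plain binomial 95% interval covered the true rate about 94% of the time at ICC 0, 87–90% at ICC 0.05 and 81–86% at ICC 0.10, across near-equal to unequal centres.

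**Step 6: the regression, conditionally.** An exchangeable logistic GEE with the uncorrected sandwich variance and a normal reference was simulated under the null (about 1,000 runs per setting, ICC 0 to 0.10). For a patient-level factor it rejected about 6–9% of the time at a nominal 5%. A bias-reduced sandwich with a t reference rejected about 4–5%.

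**The case against.** **The ICC is unknown and may be small.** This stands. At ICC 0.01 the target is met for every centre-size spread considered, and at 0.02 nearly so (7.3 to 7.6 points). Nothing in the article shows that the ICC is above 0.02–0.03, so the shortfall is conditional.

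**The centres are close to the whole population of interest.** The Sample size section says that the highest-volume centres take part and assumes that 20 clinics treat over 70% of cases. If inference is confined to these centres, the design effect does not apply in this form and the stated margin is about right. But the article justifies its precision by future programme planning, and the network has 72 clinics. That use reaches beyond the 23.

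**The number of centres may grow.** The 23 are those recruited so far. More centres for the same 150 patients would lower m and the design effect.

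**Stronger readings that the article does not support.**
- A reader might infer that the planned robust standard errors are too small. The article names no type of robust estimator, and it neither plans nor excludes a small-sample correction. That detail is commonly left to an analysis plan, which is not shown.
- A reader might expect the worst distortion for centre-level factors. The regression is described for demographic, sociomedical and clinical factors, and treatment structures are assigned to descriptive analysis under Aim 4. Centre-level covariates are not clearly in the model.
- A reader might note that under Aim 1 "The primary outcome measure for Aim 1 is treatment outcome at the end of MDR/RR-TB treatment" and compute a margin for treatment success from the 63% in the introduction. That figure is for all TB, and the article sets no precision target for success. How the primary outcome is labelled is a separate matter.
- A reader might call the calculation wrong. Every stated number reproduces.

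**Conclusion.** The concern holds in conditional form. The minimum of 129 and the 6.9-point margin are correctly computed under independence, an assumption that the same section does not keep for its regression. Allowing for centres adds roughly 0.2 points (7.1 − 6.9, ICC 0.01, equal sizes) to 2.8 points (9.7 − 6.9, ICC 0.10, CV 0.8). At ICC 0.05 the effective sample of 101 to 117 falls below the article's own minimum of 129.

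This rests on 23 centres, 150 patients, assumed ICC and CV values, and inference beyond the participating centres. It calls for a change in how precision is stated and reported; it does not show that the study is too small for a descriptive purpose. The point about GEE variance is a recommendation that applies only if the uncorrected sandwich is meant.

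**What to change.** 1. Restate the precision as a range. For example: with 150 patients in 23 centres and an observed rate of 25%, the 95% CI margin is 6.9 points without clustering, and about 7.1–7.3, 7.5–7.9, 7.8–8.4 and 8.6–9.7 points at ICC 0.01, 0.03, 0.05 and 0.10 (centre-size CV 0 to 0.8).
2. Keep the comparison of 150 with 129, but say that it secures the 7.5-point target only without material clustering (design effect up to 1.17).
3. Report the discontinuation proportion with a cluster-adjusted 95% CI, and report the estimated ICC. If inference is meant only for the participating centres, say so and keep the binomial interval.
4. As a recommendation: if the default sandwich is intended for the GEE, name a small-sample corrected version (for example Mancl-DeRouen or Kauermann-Carroll) with a t reference.

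The cost is a few sentences in the analysis plan and a software option. Enrolment, which is bounded by case numbers, does not change. The downside is a stated margin about 0.2 to 3 points less favourable, and about 6% wider again if the interval uses a t reference.
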